### ***Primary Outcome Measure***

Our primary measure of cognitive function will be the Alzheimer's Disease Assessment Scale-Cognitive-Plus (ADAS-Cog-Plus). The ADAS-Cog-Plus score is computed using a custom script using the package 'mirt' in the statistical package R ([www.r-project.org](http://www.r-project.org)). The ADAS-Cog-Plus uses a multidimensional item response theory model to generate a global cognitive functioning score and standard error of measurement for that score from the items of the ADAS-Cog and other standard cognitive assessments. For the current study, we used the 13-item ADAS-Cog, Trail Making Test Parts A and B, Digit Span Forward and Backward, and Animal and Vegetable Fluency as the input variables into the scoring algorithm. The scoring algorithm references data from the Alzheimer's Disease Neuroimaging Initiative sample, which was composed of approximately 50% MCI cases, 25% cognitively normal individuals, and 25% dementia cases. Lower scores represent better cognitive performance; specifically, ADAS-Cog-Plus scores of approximately -1.0 indicate healthy cognitive functioning, of 0.0 indicate MCI, and of 1.0 indicate dementia.

### ***Secondary Outcome Measures***

#### ***1) Executive Function***

A computerized version of the Stroop task will assess the response inhibition and selective attention components of executive function. The task will be completed using the program E-prime using a Windows-based computer and Cedrus RB-540 response pad. Color (e.g., RED, BLUE) and non-color (e.g., DISK, SCREEN) words will appear individually on the screen with 2000 ms duration and will be printed in one of three colors (blue, green or yellow). Participants are instructed to press the response pad button that is the same color as the font color of the word as quickly and accurately as possible. Following 18 practice trials, the task consists of 42 neutral trials (e.g., the word DISK printed in green font), 42 congruent trials (e.g., the word GREEN printed in green font), and 42 incongruent trials (e.g., the word GREEN printed in blue font) presented in random order. The outcome is the median response time for incongruent trials minus the median response time for congruent trials, using only trials with correct responses. Higher scores are indicative a stronger Stroop effect, and thus, poorer executive function.

#### ***2) Instrumental activities of daily living (IADLs)***

IADLs will be assessed using the self-report Lawton and Brody IADLs Scale. This scale subjectively assesses ability to telephone, shopping, food preparation, housekeeping,

laundry, mode of transportation, responsibility for own medication, and ability to handle finances.

### *3) General Balance and Mobility*

We will use the Short Physical Performance Battery to assess general mobility and balance. For the Short Physical Performance Battery, participants are assessed on performances of standing balance, walking, and sit-to-stand. Each component is rated out of four points, for a maximum of 12 points; a score < 9/12 predicts subsequent disability. We will also measure knee extension (quadriceps) strength using the method employed by the physiological profile assessment and grip strength (in kg) using a digital Jamar isometric hand dynamometer.

### *4) Mood*

Depression is a prevalent clinical entity in stroke survivors – it has been reported to be as high as 38% – and is negatively associated with cognitive function. We will use the CES-D to assess for depression, which asks participants to respond by indicating the frequency of 20 items. High scores indicate greater depressive symptoms.

### *5) Quality of Life*

We will use the EQ-5D-3L to assess health-related quality of life. The reliability and validity of the EQ-5D-3L in the stroke population have been established. Participants indicate the number of problems within the following 5 domains: mobility, self-care, usual activities, pain and anxiety/depression. A health state utility value is calculated from the scores on each of the 5 domains. Lower scores indicate poorer health state. Scores lower than zero indicate a health state considered worse than death.

*6) Health Care Resource Utilization:* Participants will complete monthly health care resource use-diaries over the 6-month study period and use this information to respond to a health care resource utilization questionnaire administered at 3 and 6 months.

### *7) Objective Sleep Quality*

We will use the MotionWatch 8© actigraphy system (MW8; camntech) a light weight, water-resistant, tri-axial wrist-worn accelerometer. The MW8 provides reliable, previously validated estimates of daytime activity and sleep quality including sleep duration (i.e., total time asleep), efficiency (i.e., actual sleep time expressed as a percentage of time in bed), and fragmentation (i.e., a measure of sleep disruption during the sleep window). Participants will be fitted with the MW8 and provided detailed information on its features (i.e., the light sensor, event marker button, and status indicator). Participants will be instructed to press the event marker button each night when they started trying to sleep; and again each morning when they finished trying to sleep. Participants also will be given consensus sleep diary and asked to complete it upon awakening each morning. We will record sleep quality with the MW8 and sleep diary over 14 days.

### *8) Blood biomarkers*

For those who decide to participate and consent to an Optional Blood Draw for Biomarkers Subject Information and Consent Form, a blood draw will be conducted at Vancouver General Hospital looking at changes in lipid profile and insulin sensitivity.

## ***Monthly Measurement of Secondary Outcome Measures***

### *1) Current Physical Activity Level*

Current level of physical activity will be determined by the valid and reliable Community Health Activities Model Program for Seniors (CHAMPS) questionnaire. This 41-item questionnaire assesses participation in various activities, including physical activities of different

intensities, for the previous 4 weeks. A metabolic equivalent (MET) is assigned to each activity. Participants will be asked to only report physical activity participation outside the research study.

#### *2) Leisure Activity Level*

Participation in leisure activity (e.g., hobbies, volunteering, etc.) will be determined by the Nottingham Leisure Questionnaire. The validity and reliability of this questionnaire in the stroke population have been established. Participants will be asked to only report leisure activity participation outside the research study.

### ***Proof-of Concept Outcome Measures***

Feasibility outcomes for delivering the intervention (i.e., adherence) will be measured throughout the 6-month intervention period. Class attendance will be recorded by the instructors.

### **Treatment Allocation and Concealment**

After patients have signed informed consent to agree to be involved in the trial, they will be stratified into 2 groups by stroke status (1 versus  $\geq 2$  prior stroke events) and then randomly allocated with an allocation ratio of 2:2:3 (EX:Cog-Plus:CON, respectively) using permuted blocks (size intentionally withheld) within each stratum. For random number generation, each stratum will have its own seed using Minitab, a statistical package to generate uniform random integers, to create the allocation order within each block. The statistician ([name]) will hold the randomization book and will give out the allocations of individual patients one-at-a-time to the 3 groups, and so these allocations will be concealed from patients, all study personnel and the investigators, except [name], until the interventions are implemented. The specific blocks will be revealed for use in the statistical analyses once the database has been cleaned and is ready for the statistical analyses. This process will allow the blocking restriction to be considered in the data analyses along with the integrity of the randomization.

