## **Statistical Analyses**

### ***Primary Outcome***

This analysis will follow the intention-to-treat principal, such that all randomized participants will be included to estimate treatment effects, irrespective of deviations from treatment protocol (e.g., loss to follow-up, non-compliance). This will be done using linear mixed models using maximum likelihood estimation. The model will include random intercepts and slopes, and fixed effects of time (baseline, month 6, month 12), treatment assignment (CON, EX, Cog-Plus), and their interaction. Baseline MMSE and ADAS-Cog-Plus scores will also be included as fixed effect covariates. Time will be specified as a categorical variable, thus allowing us to examine treatment differences at the primary endpoint (month 6) and then, as a secondary objective, whether those differences persist at the 6-month follow-up (month 12). Two planned simple contrasts will be performed using the Dunnett test. These contrasts will be employed to assess differences between: 1) the EX group and the CON group; and 2) the Cog-Plus group and the CON group. The overall alpha will be set at 0.05. A secondary complete-case analysis will be conducted using this linear mixed model, in which participants with valid data at all time points will be included. As an exploratory strategy, multiple imputation will be used to judge the impact of missingness on the conclusions drawn from this study.

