### ***Secondary & Tertiary Outcomes***

Analyses will be descriptive; no alpha has been allocated. Point and interval estimates for the effect of the intervention on each of the secondary outcomes at six and 12 months will be determined separately using linear mixed models. Multiple linear regression analyses will also be performed to explore the association between change in cognitive function, after accounting for experimental group, baseline age, baseline global cognition, and: 1) superior treatment adherence; 2) change in physical activity levels outside the research protocol; and 3) change in general balance and mobility. Randomization integrity will be determined by examining bias in the blocking sequence used to produce allocation sequence.

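### Randomisation is stratified by stroke count, but the primary model names its terms without the stratum, so analysis and design do not match; the effect on the standard error is small

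*Protocol*

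**What the plan says.** **Allocation.** In the Protocol, Treatment Allocation and Concealment, "they will be stratified into 2 groups by stroke status" (one versus two or more events). Within each stratum they are "randomly allocated with an allocation ratio of 2:2:3" by permuted blocks. The blocks are to be disclosed to the analysis once the database is clean, and the section adds: "This process will allow the blocking restriction to be considered in the data analyses along with the integrity of the randomization".

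**Primary model.** The Protocol, Statistical Analyses, Primary Outcome, specifies a linear mixed model with random intercepts and slopes and "fixed effects of time (baseline, month 6, month 12), treatment assignment (CON, EX, Cog-Plus), and their interaction". It then says: "Baseline MMSE and ADAS-Cog-Plus scores will also be included as fixed effect covariates". No other covariate is named.

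**Other analyses.** Under Secondary & Tertiary Outcomes, the secondary endpoints get linear mixed models with no stated covariates. The exploratory regressions adjust for group, age and global cognition. The only use made of the blocking is a check: "Randomization integrity will be determined by examining bias in the blocking sequence used to produce allocation sequence".

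**The concern.** Stratified allocation keeps the arms balanced on stroke count, so differences between the strata contribute little to the treatment contrast. A model without the stratum still counts those differences as unexplained variation. The usual practice is to analyse as randomised, and here the variable that restricts the allocation is the one left out.

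This is more than a detail deferred to a statistical analysis plan. The Protocol does not say that covariates will be chosen later. It names two, and neither is the stratification factor, so an analysis plan written faithfully from this section would carry the omission forward. The allocation section also raises the prospect of using the restriction in the analyses, and the analysis sections take up only the integrity check. Left open, the choice to adjust for stroke count could be made after the blocks have been revealed.

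**Working it through.** **1. The sections side by side.**

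| Place in Protocol | Use of stroke stratum or blocks |
|---|---|
| Treatment Allocation and Concealment | Defines the stratum; says the blocking restriction can be considered in the analyses |
| Primary Outcome | Time, arm, time by arm, baseline MMSE, baseline ADAS-Cog-Plus; no stratum |
| Secondary & Tertiary Outcomes | Blocks used for the integrity check; no stratum in any model |

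The omission follows from the text alone.

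**2. Inputs for its size.** The document gives neither the share of participants with two or more strokes nor any link between stroke count and outcome, so there is no plan figure to reproduce on this point. Assumptions: share f = 0.15–0.35; difference between strata d = 0.3–0.5 residual SD, after the baseline covariates. The value d = 0 cannot be excluded.

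**3. Single-endpoint approximation.** The stratum's share of residual variance is R² = f(1−f)d² / (1 + f(1−f)d²), and the standard error (SE) ratio with versus without the stratum is √(1−R²).

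- d = 0: R² = 0, ratio 1.000.
- f = 0.15, d = 0.3: f(1−f)d² = 0.1275 × 0.09 = 0.0115; R² = 0.011; ratio 0.994, a fall of 0.6%.
- f = 0.35, d = 0.5: 0.2275 × 0.25 = 0.0569; R² = 0.054; ratio 0.973, a fall of 2.7%.

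**4. Check by simulation, single endpoint.** Assumed: 120 participants, stratified 2:2:3 blocks of 7, one baseline covariate, 15% loss, 20% or 30% in the smaller stratum. The ratio of mean SEs was 1.001 for d = 0, 0.997–0.998 for d = 0.2 and 0.975–0.982 for d = 0.5, in line with step 3. The actual spread of the treatment estimate hardly moved. At d = 0.5 and 30%, its empirical SD was 0.245 without the stratum and 0.243 with it, while the mean reported SE went from 0.247 to 0.240. The term therefore changes mainly the reported SE, not the estimate.

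**5. A model closer to the one written.** The planned model has baseline as a level of time and also as a covariate. Given baseline, a stratum effect is near zero at the baseline visit and appears only later, so a single main effect dilutes it. With baseline as both response and covariate and a random intercept only, simulation gave a fall in the month-6 SE of about 0.5–1.9% from a main effect. It was about 0.9–3.2% when only post-baseline visits were responses. Separate runs of the written structure (no dropout, MMSE left out, 120 runs per scenario) gave 0.3–1.5% for the main effect and needed a stratum-by-time interaction to reach the sizes in step 3. All of these depend on the assumed covariance.

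**6. Cost in parameters.** The main effect takes 1 degree of freedom. With three time levels, the interaction adds (2−1)(3−1) = 2, for a total of 3.

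**The case against.** **The text may be read too strictly.** The allocation wording is permissive. Blocks are nested in strata, so an analysis that used the blocks would cover the stratum, and an unseen analysis plan could say how. This stands in part: the two sections are unconnected and do not flatly contradict each other. It does not remove the point, because the covariates are named and no efficacy model uses either blocks or stratum.

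**Little or nothing may be lost.** Balance comes from the allocation itself, the estimator's spread barely changes, and baseline ADAS-Cog-Plus and MMSE may absorb whatever stroke count predicts. This stands, and it is why the range must start at zero.

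**Conservative tests.** A reader might infer that tests are conservative and intervals too wide. That is the textbook expectation for a single-endpoint regression, but it is not shown for this model. In simulation of the planned structure, the reported SE was already below the empirical SD of the estimate with or without the stratum. This plausibly reflects using baseline as both response and covariate, which is a separate matter.

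**Power.** A reader might also infer that the trial is already short of its stated power. The Sample Size Calculation states power only for 39 per group, and that reproduces. With difference 2 and SD 2.85, 2/(2.85√(2/39)) = 3.10, giving power 0.87 at two-sided 0.05 and 0.80 at 0.025 per contrast. No power is stated for 34/34/52. At 0.7 SD after 15% loss (28.9 versus 44.2 completers), 0.7/√(1/28.9 + 1/44.2) = 2.93. This gives 0.83 against 1.960 and 0.76 against a Dunnett value of 2.222. How multiplicity enters the sample size is a different question.

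**Conclusion.** The point holds as a mismatch between design and analysis. Allocation is stratified by stroke count, the primary model names its terms without the stratum, and no other section puts it into an efficacy model. The omission does not bias the treatment estimate.

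The consequence is small. The effect on the reported SE is nil if stroke count does not predict outcome given the baseline covariates, and roughly 0.5–3% if a difference of 0.3–0.5 SD remains. That range rests on an assumed stratum share, an assumed residual difference and an assumed covariance, none of which the document gives. The omission itself is certain; the size of the harm is not. The change is worth making because it is nearly free and settles the adjustment before the blocks are revealed. The case for it does not rest on claims about conservatism or about power.

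**What to change.** - Add stroke stratum, as randomised (one versus two or more), to the primary model as a fixed effect with its interaction with time. If the model is set up with only post-baseline visits as responses, a main effect is enough.
- Carry the same term into the secondary-outcome, complete-case and multiple-imputation models.
- Reconcile Treatment Allocation and Concealment with Statistical Analyses, Primary Outcome: state that the stratum is the way the restriction enters the efficacy analyses, and whether the blocks serve only the integrity check.
- Settle this before the allocation blocks are disclosed.

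The cost is one to three degrees of freedom. The variable is already recorded at randomisation, so no new data and no extra participants are needed.

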### **Interventions**

All exercise-based classes will be led by instructors who have formal expertise in delivering group exercise programs to older adults. All classes will be 60 minutes in duration. All classes will have a maximum participant to instructor ratio of 4:1. Class attendance will be recorded by the instructors. To minimize contamination, only one class will occur at any given time in the same facility. In addition, there will be a minimum of 30 minutes between classes at any given facility. All intervention groups will include twice-weekly classes of 60 minutes each over 26 weeks. Fidelity across instructors and across time will be ensured by providing instructors with detailed protocols including pictures; regular observation and intervention classes by study PI and coordinator and auditing with standard checklist to ensure intervention content is delivered accurately and consistently; and videotaping classes from each intervention arm across time.

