### ***Cog-Plus Group***

We have designed this program based on the feedback received from our pilot study and based on current evidence. In addition, we aimed to design a program that could feasibly be implemented in the community with minimal resources. Because impairment in multiple cognitive domains is common following stroke, the cognitive exercises included in the program targeted various aspects of cognition, including learning and memory, processing speed, attention, working memory, and executive functions. Each class will begin with the participants being asked to memorize a 7-item word list. Next, each participant will complete approximately 15 minutes of the brain training program Lumosity using an individually-issued Apple iPad. Lumosity consists of various short games (typically 1 to 5 minutes) that target various aspects of cognition (e.g., working memory, divided attention, processing speed). Each class, participants will be encouraged to complete at least 5 distinct games. For the remaining class time (approximately 30 minutes), the participants will complete a variety of social games and mental activities in pairs or as entire class. Some of these activities will utilize apps on the Apple iPads (e.g., *Heads-Up*, *Teledoodle*), and others are based on improvisation and mental activities from the PERK program^64. At the end of class, participants will recall as many of the words from the word list; they will use the Notes program on the iPad to record the recalled words. Approximately every month, the class instructor will meet individually with the participants to show performance progress on the Lumosity training program and to discuss outstanding concerns and areas of improvement (e.g., short-term memory, speed of responding). Every month, the 7-item word list will be replaced with a 15-item word list, and participants will be requested to recall those words immediately, as well as at the end of the class.

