### ***CON Group***

The CON program will follow the protocol used in [name] previous RCT. The CON protocol will consist of stretches, deep breathing and relaxation techniques, general posture education, general core control exercises, grip strength and dexterity exercises, and light

isometric toning exercises. Some exercises from the EX program will also be included but in a simplified format without progression (e.g., double calf raises, heel and toe tapping, balance exercises). Once a month, the class will consist of educational lecture and will include topics such as sleep hygiene, goal setting, and nutrition. This group will serve to control for confounding variables such as physical training received by traveling to the community centre for twice-weekly classes and changes in lifestyle secondary to study participation. The Timed-Up-and-Go task will be completed on a monthly basis to allow for objective physical performance tracking.

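### Every arm is taught in small classes but the primary model has no class term, so intervals are too narrow if classmates' outcomes are correlated

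*Protocol*

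**What the plan says.** Randomization is individual. Under Treatment Allocation and Concealment, the statistician will "give out the allocations of individual patients one-at-a-time to the 3 groups".

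Delivery is in groups in every arm. The Interventions section states: "All intervention groups will include twice-weekly classes of 60 minutes each over 26 weeks". It also states: "All classes will have a maximum participant to instructor ratio of 4:1". The CON Group section confirms that control is a class too: "Once a month, the class will consist of educational lecture". In the Cog-Plus Group section, for about half of each hour, "the participants will complete a variety of social games and mental activities in pairs or as entire class".

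There is more than one instructor, and differences between them are addressed through training and oversight: "Fidelity across instructors and across time will be ensured by providing instructors with detailed protocols including pictures", followed by observation, audit and video recording.

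The Primary Outcome part of Statistical Analyses lists the model: "The model will include random intercepts and slopes, and fixed effects of time", then treatment, the time-by-treatment interaction, and baseline MMSE and ADAS-Cog-Plus as covariates, fitted by maximum likelihood. Two Dunnett contrasts against CON follow, at an overall alpha of 0.05. No class or instructor term, cluster-robust variance or clustering sensitivity analysis is named. The Sample Size Calculation has no design effect. The only design structure held over for the analysis is the randomization blocking, which is not class membership.

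**The concern.** By month 6 a participant will have been offered 2 × 26 = 52 sessions with a small group and one or more instructors. Shared teaching, group pace and, in Cog-Plus, planned interaction between classmates are plausible reasons for their outcomes to resemble each other. The arms have different content, so a class sits within one arm, and any variation between classes becomes part of the difference between arms.

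Random intercepts and slopes, read in the usual way as belonging to the participant, deal with repeated measures on one person. They do not deal with correlation between two people in the same class. If that correlation is positive, the stated model gives standard errors that are too small for both primary contrasts. A few lively classes could be taken for a treatment effect more often than the stated alpha allows.

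The larger trial is also affected. The Introduction says the results will inform its design, and that trial would need a class ICC, which this plan does not estimate.

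**Working it through.** **Inputs from the protocol.** Mean changes of 3 and 1 points (difference 2), SD 2.85, alpha 0.05, 39 per group; standardized effect 0.7 for ADAS-Cog-Plus; 34 / 34 / 52 randomized (Sample Size Calculation); two Dunnett contrasts at overall alpha 0.05 (Primary Outcome).

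**Assumptions, because the protocol does not give them.** m = 4 people per class (from the 4:1 ratio), stable class membership, equal ICC in all arms, ICC of 0.01 to 0.10, two-sided testing.

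**Step 1: the plan's own figure.** Per group, n = 2 × (z for alpha + z for power)² × (SD / difference)².
- Two-sided 0.05: 2 × (1.960 + 0.842)² × (2.85 / 2)² = 31.9, so 32.
- Two-sided 0.025 (0.05 split over two contrasts): 2 × (2.241 + 0.842)² × (2.85 / 2)² = 38.6, so 39.

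With 39 per group and the Dunnett critical value of 2.212, power for one contrast is 0.812. The stated 39 per group with power above 0.80 is reproduced, for independent participants.

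**Step 2: error when class correlation is ignored.** At 34 / 34 / 52 the two contrasts share the control arm and have correlation 34 / (34 + 52) = 0.395. The Dunnett critical value is then c = 2.222, which gives 5.0% under independence. With correlated classmates the true variance of each contrast is larger by DE = 1 + (m − 1) × ICC. The actual family-wise error is P(max |Z| > c / √DE).

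| ICC (m = 4) | DE | SE should be larger by | c / √DE | Coverage of an unadjusted 95% interval | Family-wise error | Simulated |
|---|---|---|---|---|---|---|
| 0.01 | 1.03 | × 1.015 | 2.19 | 94.7% | 5.4% | 5.6% |
| 0.05 | 1.15 | × 1.07 | 2.07 | 93.2% | 7.2% | 7.3% |
| 0.10 | 1.30 | × 1.14 | 1.95 | 91.4% | 9.6% | 9.6% |

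The simulation (60,000 trials per row) generated class effects and analysed participants as independent.

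**Step 3: power if clustering is allowed for.** For one Dunnett contrast at effect 0.7, before attrition, the expected test statistic is 0.7 / √(1/34 + 1/52) = 3.174 under independence. Power is Φ(3.174 / √DE − 2.222): 0.829 at ICC 0, 0.770 at 0.05 and 0.713 at 0.10. Keeping the information of 120 independent participants would take 120 × 1.15 = 138 or 120 × 1.30 = 156.

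**Step 4: sensitivity to m.** At ICC 0.05, family-wise error is about 10% if 8 people share a class or instructor, and about 14% if 12 do. The protocol describes neither case.

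**The case against.** The opposing case has several parts.

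- **The statistical analysis plan may cover it.** Only the protocol is at hand. It does not state the level of the random effects, the covariance structure or the degrees-of-freedom method, and it nowhere says participants are independent. So it would be wrong to call the model fully specified. What remains is that the protocol lists the primary model's terms, and applying that list makes no allowance for classes.
- **Correlation is not shown.** This stands. Fidelity procedures exist to reduce differences between instructors and are not evidence that differences remain. Cog-Plus also includes individual tablet training, word recall and monthly individual meetings, so peer interaction is only part of the treatment. The conclusion must be conditional on a positive correlation.
- **Instructors may teach several arms.** A reader might infer that instructors, like classes, are nested within arm and that their effects pass in full into both contrasts. The protocol does not say so. It describes the instructors of all exercise-based classes together, and CON reuses some EX exercises. If the same people teach both, instructor effects partly cancel in EX-CON.
- **Class membership may change.** No fixed class groups are described, and participants are allocated one at a time. With movement between classes, m is less well defined and the design-effect formula is only a guide.
- **This is a proof-of-concept trial.** It is, but the Sample Size Calculation says it is designed to evaluate statistical significance, and an overall alpha is set.

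**Conclusion.** The point holds in conditional form. Classes are nested within arm, the listed primary model has no class term, and the sample size has no design effect. For any positive correlation between classmates at month 6, both primary contrasts have intervals that are too narrow and the Dunnett procedure exceeds 0.05.

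With four per class and stable membership, family-wise error runs from about 5.4% to 9.6% over ICC 0.01 to 0.10. At the low end this is minor. It would be larger if more people share a class or an instructor.

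A reader might go further and conclude that error is known to be well above 10%, or that alpha is certainly not held. The protocol does not support either. The first needs larger groups than the 4:1 ratio implies, or a higher ICC than assumed here, and the second needs proof that the correlation is positive. The change is worth making because it is cheap, not because large inflation has been shown.

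**What to change.** 1. Instructors already record attendance. Add class group and lead instructor to that record.
2. Add to the primary model a random effect for class at the post-baseline visits. Where membership changes, use the class mainly attended. Use small-sample degrees of freedom, for example Kenward-Roger, which means fitting by REML instead of the stated maximum likelihood.
3. Base the two Dunnett contrasts on this model.
4. Report the estimated class ICC for use in planning the definitive trial.
5. Add a sensitivity analysis with clustering by instructor, since an instructor may lead several classes or teach more than one arm.

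**Cost.** One field on an existing form, one model term and a change of fitting method. Intervals will be slightly wider if class effects exist. The class variance will be imprecisely estimated: at four per class there are about 34 / 4 = 8 to 9 classes in each of EX and Cog-Plus, and 52 / 4 = 13 in CON. If the variance is estimated as zero, the random-effects structure reduces to the planned one.
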